### Sample size

A sample size of 76 patients would have 80% power to detect a difference in preference rates of 30% between the two dentures (30% vs 60%) at a significance level of 5%, assuming that 10% of patients express no preference; 67 patients would be required to detect a different of 30% (25% vs 55%) assuming 20% express no preference. A total of 85 patients will be recruited overall to allow for a dropout rate of around 10%, consistent with previous studies.

### Statistical analysis

Preference results will be presented as a 2 × 2 table for paired data and analysed using McNemar’s test for paired data to estimate the difference in proportions of patients preferring dentures made from alginate impressions compared to those made from silicone impressions, prior to any denture adjustment. Those patients expressing a preference will be allocated to the discordant cells of the table and those expressing no preference will be allocated to the concordant cells according to whether they felt that both sets of dentures were either satisfactory or unsatisfactory. The difference in proportions will be presented with a 95% confidence interval.

OHIP–EDENT scores at the end of each adjustment period will be analysed using an ANOVA model appropriate for an AB/BA crossover design. The model will incorporate denture, period, and subject, all as fixed effects. The difference between the dentures will be estimated with 95% confidence intervals.

Differences between Likert scores (measuring comfort, mobility, chewing efficiency, comfort of impression taking, taste and preference of impression taking) for each denture will be calculated and compared using the Wilcoxon test for matched pairs.

All analyses will be conducted on the intention-to-treat (ITT) population where patients will be analysed according to the treatment they were randomised to, and the per-protocol population (if necessary), where patients will be included according to the treatment they received.

An additional analysis will test whether the differences in comfort, mobility and chewing efficiency between the two dentures varies according to the timing of the assessment (i.e. between the adjustment and confirmation periods). The 5-point Likert questionnaires are completed after adjustment period 1 (wearing the yellow denture), and also at the end of adjustment period 2 (wearing the green denture). The confirmation period requires patients to complete the 5-point Likert questionnaire side-by-side after wearing whichever denture they preferred during the 2-week period. Wilcoxon tests for matched pairs will be performed on the difference in scores between the two dentures in the adjustment and confirmation periods.

Only patients who wore and completed the assessment for both dentures in the confirmation period will be included in this analysis.

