**Figure 1 F1:**
[figure not shown]
IMPROVDENT Trial Flow Diagram.

The initial randomisation occurs at the baseline visit using sealed envelopes to determine which tray is used to make the first impression and which impression material is used first (silicone or alginate). Envelopes are created by the trial statistician, using random block sizes, and are stored in a secure randomisation locker. The habituation randomisation occurs at the completion of denture construction to determine the colour marking (red or blue) of the dentures (silicone red/alginate blue or alginate red/silicone blue, the red denture to be tested first during habituation period). Randomisation will be via sealed envelopes created by the trial statistician. Randomisation will be blocked (random block size) to ensure balance between groups. Sealed envelopes will be stored in the secure randomisation locker.

The aim of the adjustment randomisation is to establish the order of testing during adjustment. This final randomisation will occur at the conclusion of the habituation period to determine the colour re-marking (yellow or green) of the dentures (silicone yellow/alginate green, alginate yellow/silicone green, yellow to be tested in adjustment period 1 and green to be tested in adjustment period 2). Randomisation will be blocked (random block sizes) and balanced for order of testing in the habituation period. Randomisation will be administered by telephone by CTRU, using an automated 24-hour telephone system.

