### Habituation period (2 weeks)

Once dentures have been constructed, patients will be given both sets of dentures for a 2-week habituation period. The habituation period serves a dual purpose: firstly to allow patients to try both sets of unadjusted dentures to establish whether one set is preferred. Secondly, it has been suggested in a previous crossover study
[19] that patients tend to prefer the denture given in the second period because the first period is spent habituating to the feel of the new dentures which may feel very different to their old dentures. Thus by allowing a habituation period in this study it is hoped that patients will be used to the feel of the new dentures prior to the two adjustment study periods. During the 2 weeks the patients will be provided with a diary and asked to record the wearing of each set of dentures. Within the diary there is a randomised and structured programme alternating the use of the red and blue dentures with an opportunity for patients to provide qualitative feedback regarding the impact on behaviour and interactions in social settings wearing the new dentures. On the first day, they will be asked to wear the red denture; on the second day the blue denture. This initial period of alternation is to avoid familiarity and habituation clouding the later assessment. After 2 days they will be guided to wear the red-coded denture for 3 days followed by the blue-coded denture for 3 days. They will then be asked to frequently alternate the dentures for 2 days. Finally, for the last 4 days of the 2-week habituation period, they will be asked to wear whichever denture they prefer. On return to clinic they will be asked to report their preferred denture. If they have no preference they will be asked if this is because they were satisfied by both sets of dentures or if it is because both sets are unsatisfactory. They will then be asked to score each denture for comfort, mobility and chewing efficiency using a 5-point Likert scale and will complete a health economics questionnaire. Both sets of dentures will be returned and re-marked with a yellow or green spot by the Head of the Prosthodontic Research Laboratory (or designee).

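### The primary preference test pools over the randomised wearing order; an order-stratified test would cost nothing and guard against an order effect that the protocol itself discusses

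*Protocol article*

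**What the plan says.** - **Primary analysis** (Statistical analysis): preference before adjustment goes to McNemar's "test for paired data to estimate the difference in proportions of patients preferring dentures made from alginate impressions" against silicone. Patients with a preference fill the discordant cells and those without fill the concordant cells. "The difference in proportions will be presented with a 95% confidence interval". Wearing order is not mentioned.
- **Order** (Randomisation and blinding): which material is marked red is randomised in random-sized blocks, "the red denture to be tested first during habituation period".
- **Wearing programme** (Habituation period): red 1 day, blue 1 day, red 3 days, blue 3 days, frequent alternation for 2 days, then free choice for 4 days. Preference is asked on return to clinic.
- **Order effect** (Habituation period): an earlier crossover study suggested that "patients tend to prefer the denture given in the second period", because the first period goes on getting used to new dentures. The Discussion calls this a potential bias to guard against.
- **Secondary OHIP-EDENT analysis** (Statistical analysis): "The model will incorporate denture, period, and subject, all as fixed effects".

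**The concern.** The trial randomises and balances wearing order, and its primary analysis then ignores it. The habituation period is intended to dispose of the second-denture effect before the two adjustment periods. The primary preference, however, is recorded at the end of habituation, the phase in which the protocol says patients are still adapting. The plan therefore adjusts for period after habituation, and not where its own reasoning makes an order effect most plausible.

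If order matters, each patient's preference has a predictable part that depends on which denture came first. Pooling counts that part as noise, so the standard error is too large. If the two orders end up with unequal numbers, a fraction of the order effect also passes into the estimated material difference.

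**Working it through.** **Inputs.** From Sample size: 76 patients for 80% power, with 30% preferring one denture and 60% the other, "at a significance level of 5%, assuming that 10% of patients express no preference". Two-sided testing is inferred because it reproduces the stated numbers. *Assumption, not in the documents:* an order effect δ, the proportion preferring the second-worn denture minus the proportion preferring the first-worn, set at 0, 0.2, 0.3 and 0.4. With materials equal and 10% without preference, the share of those with a preference who favour the second denture is (0.45 + δ/2)/0.9, which is 61%, 67% and 72% for δ = 0.2, 0.3 and 0.4.

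**1. The plan's own figure.** With discordant proportion p and difference d, n = [1.96√p + 0.8416√(p − d²)]²/d².
- 30% v 60%: p = 0.9, d = 0.3, so [1.96√0.9 + 0.8416√0.81]²/0.09 = 76.1 (stated 76).
- 25% v 55%: p = 0.8, d = 0.3, so [1.96√0.8 + 0.8416√0.71]²/0.09 = 67.4 (stated 67).

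Both figures reproduce, and neither allows for order.

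**2. Effect of pooling, orders 38/38.** The silicone-minus-alginate difference is d + δ when silicone is second and d − δ when it is first. The average within-order variance is p − d² − δ², whereas pooling uses p − d². For n = 76, p = 0.9, d = 0.3:

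| δ | pooled SE √(0.81/76) | true SE √((0.81 − δ²)/76) | ratio |
|---|---|---|---|
| 0 | 0.1032 | 0.1032 | 1.00 |
| 0.2 | 0.1032 | 0.1007 | 1.03 |
| 0.3 | 0.1032 | 0.0973 | 1.06 |
| 0.4 | 0.1032 | 0.0925 | 1.12 |

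In simulation the average estimated pooled SE is slightly smaller (about 0.1025), so the excess is 2%, 5% and 11%, with interval coverage of 95.0%, 95.6% and 96.6%.

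**3. Type I error of McNemar's test (45% v 45%).** This is 2[1 − Φ(1.96√(0.9/(0.9 − δ²)))], which gives 5.0%, 4.5%, 3.9% and 3.1% for the four values of δ. Simulation gives 4.9%, 4.3%, 3.9% and 3.1%; Prescott's test stays between 4.9% and 5.1%.

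**4. Power at 30% v 60%.** For McNemar's test, Φ[(0.3√76 − 1.96√0.9)/√(0.81 − δ²)] gives 80.0%, 80.6%, 81.4% and 82.6%. Simulated power:

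| δ | McNemar | Prescott | gap (points) |
|---|---|---|---|
| 0 | 80.2% | 80.0% | −0.2 |
| 0.2 | 80.5% | 82.0% | about 1.5 |
| 0.3 | 81.3% | 84.6% | about 3 |
| 0.4 | 82.9% | 88.5% | about 6 |

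A repeat simulation gave McNemar 80.4%, 81.7% and 82.4% against Prescott 81.9%, 84.8% and 88.2% for δ = 0.2, 0.3 and 0.4.

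**5. Unequal orders.** The pooled estimate shifts by δ(n₁ − n₂)/n.
- 37/39: 2δ/76 = 0.5, 0.8 and 1.1 points for δ = 0.2, 0.3 and 0.4.
- 34/42: 8δ/76 = 2.1, 3.2 and 4.2 points. Simulated type I error is still 4.7% to 4.8%.

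If 85 patients split 43/42 and 9 drop out at random, the expected imbalance is about 2.3 patients, and an imbalance of 8 or more has probability about 1.5% (hypergeometric).

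**The case against.** A reader might infer that the protocol expects patients to favour the second denture in the primary outcome. It does not say so. It reports a suggestion from an earlier study with consecutive periods, and it gives the opening alternation the purpose of keeping habituation from clouding the assessment. Six of the 14 days, immediately before the question, are alternation or free choice. Whether any order effect survives that is unknown. This objection stands, and it is why every size here is conditional.

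A reader might also infer that the trial is underpowered or its error rates wrong. The figures do not support that. McNemar's power does not fall below the plan, type I error is not inflated, and with balanced orders the estimate is unbiased. At δ = 0.2 the pooled interval covers 95.0%. The loss is only relative to a better test.

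The 34/42 split is extreme. Order is assigned at completion of denture construction and the outcome follows two weeks later, so earlier dropout cannot unbalance it. The contrast with OHIP-EDENT is also imperfect: that score comes from two sequential 8-week periods, whereas preference is one joint judgement.

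Finally, an order-adjusted sensitivity analysis may be in the analysis plan, which is not shown. But the protocol itself names the primary test, and that test takes no account of a factor the trial randomised.

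**Conclusion.** The point holds as an efficiency and robustness improvement that should be made. It is not a threat to validity. McNemar's test is legitimate and matches the sample size. If an order effect of 0.2 to 0.4 remains, it is conservative (type I error about 4.3% down to 3.1%), its interval is about 2% to 11% too wide, and it gives up about 1.5 to 6 points of power. Realistic imbalance moves the estimate by about 1 point or less. With no order effect nothing is lost either way. These sizes rest on an additive order effect whose magnitude is assumed, on 76 analysed patients, and on the protocol's own preference rates.

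**What to change.** Before unblinding, specify:

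1. **Primary test:** Prescott's test, which keeps patients without a preference as a middle category, or the Mainland-Gart test, stratified by habituation order.
2. **Estimate:** the average of the two order-specific differences (silicone minus alginate), D = (D₁ + D₂)/2, with SE = ½√(V₁/n₁ + V₂/n₂), where Vₖ = pₖ − Dₖ² and pₖ is the proportion with a preference in order k. Report its 95% confidence interval. The simple normal interval covered about 94% in simulation, so name the interval method.
3. **Sensitivity analysis:** McNemar's test as now written.
4. **Adjusted preference:** the same approach, by adjustment order.

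The cost is a change of wording and a few lines of code, with no new data and no change to the sample size. Trial status reports recruitment closed in April 2012 with results expected in 2013, so the change is open only if the preference data have not yet been unblinded.

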### Denture construction

The Prosthodontic Research Team at LDI has developed and published a method of producing two or more sets of dentures which are clinically similar apart from the one deliberate alteration which is to be the subject of an RCT
[16]. This methodology will be used to produce two sets of dentures which are clinically similar apart from the impression material that was used to provide the mould for the fitting surface of each denture.

The intervention at the clinical secondary impression stage is the subject of this study; the secondary impressions will be made with either alginate or silicone. To take the secondary impressions, two sets of similar, spaced (2 mm), unperforated, light-cured acrylic secondary impression trays will be constructed. A set of impression trays consist of an upper and a lower tray; each set will be numbered in the laboratory A or B. Clinically, the secondary impression trays will be trimmed to size in the mouth to remove any over extension. After trimming, the trays will be randomly allocated to either the alginate or silicone impressions. The impression trays allocated to the alginate side of the study will be ‘border moulded’ with greenstick compound in the standard way
[17] and alginate (Xantalgin®) impressions taken. The trays allocated to silicone will be ‘border moulded’ with silicone (express 3 M) and impressions taken with silicone (express 3 M). The order in which the impressions are taken will be randomised; the patients will be rested for comfort for approximately 30 minutes between taking the first set of impressions and taking the second set of impressions. If a clinically adequate impression is not achieved at the first attempt with either material the impression will be repeated, until clinical adequacy is achieved. The total time taken to make the impression and number of attempts will be recorded.

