### Outcome measures

The co-primary outcome measures of the trial are patient expressed preference for unadjusted dentures and cost-effectiveness.

Secondary outcome measures are patient preference for adjusted dentures, patient assessment of comfort and taste (using a 5-point Likert scale) and preference of the impression materials, patient assessment of comfort, mobility, chewing efficiency of the dentures (using 5-point Likert scales).

Patient preference for dentures will be established by asking whether one or other denture is preferred, or whether there is no preference. Those expressing no preference will be further asked whether both dentures were satisfactory or unsatisfactory. Patients will be asked to reflect on the whole process of receiving the final denture (including initial comfort, amount of adjustment needed) when expressing preference for the adjusted denture.

Health-related quality of life will be measured using the OHIP-EDENT questionnaire
[18]. This questionnaire is adapted from the Oral Health Impact Profile (OHIP) and is particularly suitable for edentulous patients.

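### The adjustment-period Likert scores are tested without the period term that OHIP-EDENT receives from the same visits, which costs power on these secondary outcomes if a period effect remains

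*Protocol article*

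**What the plan says.** All references are to the protocol article.

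- **OHIP-EDENT** (Statistical analysis): scores at the end of each adjustment period go into an ANOVA for an AB/BA crossover. "The model will incorporate denture, period, and subject, all as fixed effects".
- **Likert items** (Statistical analysis): one rule covers denture and impression items alike. "Differences between Likert scores (measuring comfort, mobility, chewing efficiency, comfort of impression taking, taste and preference of impression taking") are calculated "for each denture will be calculated and compared using the Wilcoxon test for matched pairs". No period or order term is named.
- **Timing of the denture ratings:** "The 5-point Likert questionnaires are completed after adjustment period 1 (wearing the yellow denture), and also at the end of adjustment period 2", the same visits at which OHIP-EDENT is completed (Adjustment period 1, Adjustment period 2, Assessments). Habituation ratings of both dentures are given at one clinic visit, and confirmation ratings are made side by side.
- **Order:** for the adjustment periods, "Randomisation will be blocked (random block sizes) and balanced for order of testing in the habituation period" (Randomisation and blinding, text at Figure 1). For the impressions, "The order in which the impressions are taken will be randomised" (Denture construction).
- **Second-period preference:** the Habituation period section cites an earlier crossover study suggesting that "patients tend to prefer the denture given in the second period because the first period is spent habituating" to new dentures. The habituation period was added in the hope of preventing this.
- **Impression outcomes** (Outcome measures): "patient assessment of comfort and taste (using a 5-point Likert scale) and preference of the impression materials".

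**The concern.** Two outcomes collected from the same patients at the same two visits are analysed differently, and no reason is given. The OHIP-EDENT model separates any difference between the first and second adjustment period from the difference between dentures. The matched-pairs test does not. A patient who wears silicone second contributes the denture effect plus the period effect, and a patient who wears silicone first contributes the denture effect minus the period effect. With equal sequences the period effect cancels from the average, but it stays in the spread and is treated as noise. With unequal sequences part of it also enters the average. What is at stake is power on the comfort, mobility and chewing scores, and similarly on impression comfort and taste, where the randomised order of impressions is not used.

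A smaller matter concerns impression preference. Outcome measures attaches the 5-point scale to comfort and taste and lists preference after it without a response format. Statistical analysis counts preference among the Likert scores. The test can only be checked once the format is known.

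**Working it through.** **1. The plan's own figures.** The article gives a sample size only for denture preference. With discordant proportion pD and difference d, McNemar's test at two-sided 5% and 80% power needs

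n = [1.96·√pD + 0.8416·√(pD − d²)]² / d²

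- 60% vs 30%: pD = 0.90, d = 0.30, n = 76.09 (stated 76).
- 55% vs 25%: pD = 0.80, d = 0.30, n = 67.36 (stated 67).
- 76 / 0.9 = 84.4, rounded up to 85 (stated 85).

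These reproduce, and this point does not affect them. No power is claimed for the Likert scores.

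**2. Assumptions for the Likert scores.** From the article: 76 analysed patients, a 5-point scale, an AB/BA order. Not in the article, so assumed: scores cut from a standard normal latent variable at −1.5, −0.5, 0.5 and 1.5; within-patient correlation 0.5; denture effect 0.35 latent SD; period shift from 0 to 1.0 latent SD.

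**3. Simulation, balanced order (38/38), 4,000 runs per cell.** The signed-rank test on denture differences is compared with a rank-sum test on period differences between sequences.

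| Period shift (SD) | Type I error: signed-rank | Type I error: period-adjusted | Power: signed-rank | Power: period-adjusted |
|---|---|---|---|---|
| 0 | 4.9% | 4.8% | 78% | 77% |
| 0.25 | 4.3% | 5.1% | 76% | 77% |
| 0.5 | 2.8% | 4.7% | 72% | 77% |
| 1.0 | 1.0% | 4.9% | 48% | 72% |

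Simulation error at a power of 75% is √(0.75 × 0.25 / 4000), or 0.7 points, so gaps of about 1 point are near the noise. Repeat runs at other shifts gave 74–77% against 75–79% at 0.3 SD (a gap of 1 to 2 points within each run), and 55–59% against 70–74% at 0.8 SD (15 to 17 points). At 0.5 SD the gap was 5 to 6 points in every run.

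**4. Check by hand on the latent scale.** The within-patient difference has variance 2 × (1 − 0.5) = 1. Under balanced order a shift π adds π² to the variance that the unadjusted test sees, while the mean difference is no more variable than before. The effective critical value is therefore 1.96·√(1 + π²), and power is about Φ(0.35·√76 − 1.96·√(1 + π²)), with 0.35·√76 = 3.051.

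- π = 0: Φ(1.091) = 86.2%.
- π = 0.3: Φ(1.005) = 84.3%, a loss of 2.0 points.
- π = 0.5: Φ(0.860) = 80.5%, a loss of 5.7 points; type I error 2·Φ(−2.191) = 2.8%.
- π = 0.8: Φ(0.541) = 70.6%, a loss of 15.7 points.

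Power is higher throughout than in the simulation because the latent scale is not cut into five categories, but the losses agree.

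**5. Unequal sequences.** The mean denture difference is shifted by π × (n₁ − n₂)/n. At 42/34 and π = 0.5 this is 0.5 × 8/76 = 0.053 SD. When it works against the better denture, signed-rank power is 70% at 0.25 SD and 56% at 0.5 SD, against 77% and 76% adjusted. Type I error stays at 3.5% to 4.8% across the shifts. At 46/30 it reaches 6.2%, 9.8% and 16% at shifts of 0.25, 0.5 and 1.0 SD.

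**6. Which ratings are affected.** Adjustment-period scores have a period 2 minus period 1 difference. Impressions are each taken in a randomised first or second place, so comfort and taste have an order, although both are rated afterwards together. Habituation ratings follow repeated alternation and four days of free choice and are given at one visit. Confirmation ratings are side by side. Neither of these two has a period difference to use.

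**The case against.** A matched-pairs Wilcoxon test on within-patient ordinal differences is a standard test and is valid under balanced order. The habituation period is there to remove the second-period effect before adjustment begins, so the remaining shift may be small. At 0.3 SD the gain from adjusting is only 1 to 2 points, and no figure in the article supports 0.8 SD. The outcomes are secondary and no power is claimed for them. All of this stands and limits the weight of the point. It does not explain why period is kept for OHIP-EDENT and dropped for scores from the same visits.

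Four stronger readings are tempting, and the document does not support them.

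- **The test inflates false positives.** With balanced order it does the reverse. Inflation appeared only at 46/30. With 85 randomised and 9 lost, that needs a 46/39 split despite blocking and every loss from the smaller sequence. Even 42/34, from a 43/42 split, needs 8 of 9 losses on one side.
- **The protocol forecasts a period effect.** It cites one from earlier work and presents habituation as the guard against it.
- **All Likert ratings need adjustment.** Habituation and confirmation ratings are not separated by period.
- **The impression-preference analysis cannot be run.** No section says that it is a single choice, and Statistical analysis calls it a Likert score. If it is rated per material, the paired test works. If it is a plain choice, there is no pair of scores to subtract. Only the unclear format is established.

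**Conclusion.** The point holds as an efficiency weakness in secondary analyses. The Likert test for the adjustment periods, and for impression comfort and taste, leaves out a randomised order that the OHIP-EDENT model uses for period. The planned test is valid under balanced order but conservative if a period effect remains. The sizes of loss in the working rest on the assumed correlation, denture effect and period shifts, none of which the article gives. The losses grow if the analysed sequences become unequal against the better denture. The co-primary preference analysis and the sample size are untouched. The mismatch on impression preference is a minor matter of wording.

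**What to change.** - **Adjustment-period comfort, mobility and chewing:** compare period 2 minus period 1 differences between the two sequences with a Wilcoxon rank-sum test and a Hodges-Lehmann estimate, or fit an ordinal model with denture and period.
- **Impression comfort and taste:** apply the same approach by randomised impression order.
- **Habituation and side-by-side confirmation ratings:** keep the matched-pairs test.
- **Impression preference:** state the response format, reconcile Outcome measures with Statistical analysis, and match the test to it. Keep the paired test if there is a score per material; if it is a choice, use an analysis like the one for denture preference.

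The cost is a change of analysis wording. The orders are already randomised, and no new data or patients are needed. If there is no period effect, the adjusted test gives up about 1 point of power (77% against 78% in the table).
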